## Data collection and management

### Plans for assessment and collection of outcomes {18a}

All questionnaire measures will be collected using REDCap [38, 39]. Participants will receive automatic reminders sent after 4 and 8 days. If participants have not completed the questionnaires after receiving reminders, a member of the research team will contact them by phone in an attempt to re-engage them.

For post-treatment and follow-up measures, contact will be attempted a maximum of 3 times in total at different time points to prompt completion.

### Plans to promote participant retention and complete follow-up {18b}

If a participant is inactive (e.g., did not log in to the platform) for more than 10 days, the therapist will initially contact the participant through the chat function on the platform. The purpose of this contact is to assess the reasons for inactivity and to schedule a motivational conversation with the participant and their parents if necessary.

If the participant does not respond to the chat messages within 2 days, the therapist will contact them by telephone to assess the reasons for inactivity and schedule a motivational conversation. These conversations may last up to 45 min and aim to help the participant identify reasons for change and address potential treatment barriers.

The participant will be encouraged to continue working with the program during these conversations. However, if inactivity persists, the participant will be discontinued from the treatment and assisted in finding a more suitable treatment option.

All participants enrolled in the study will receive the post- and follow-up measures, unless they specifically decline participation in these. Therefore, even participants who do not complete the treatment will still be assessed with all measures.

### Data management {19}

The data will be collected in REDCap and MindDistrict, the data will be stored in the REDCap database or on SharePoint during and after the trial. Every 6 months, a data control will be carried out to make sure the data appears as expected. In REDcap, there are inbuilt validations for the questionnaires, and all questions are required to be answered to complete the questionnaires.

### Confidentiality {27}

Any personally sensitive information is processed by Center for Digital Psychiatry and Aarhus University in personally identifiable form for as long as it is necessary for the research purpose. The storage of information complies with responsible research practice and general data protection regulation. Once the information is no longer necessary for the research project, it will be anonymized or deleted. During this trial, no personally sensitive information will be shared, and all data will be anonymized before publishing the results.

## Statistical methods

### Statistical methods for primary and secondary outcomes {20a}

The primary analysis are the association between the change in SCAS-C/P total score from pre- to post-treatment and trial condition will be analyzed using linear mixed model regression.

For the secondary analysis, the association between YODA, dichotomized as YODA total score ≥ 1 vs. YODA total score < 1, and the three trial conditions at post-treatment will be analyzed using logistic regression.

A more detailed analysis plan will be developed prior to the end of recruitment for both primary and secondary analyses in collaboration with a statistician employed at the participating organizations.

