### Sample size {14}

The sample size calculation is based on scenarios of difference between treatment and waitlist at end of treatment for the primary outcome SCAS, based on Stjerneklar and colleagues [32] previous study detecting a difference of 10 points between the waiting list and the (combined) treatment groups in change in SCAS score from baseline to 3 months’ follow-up. Using a linear mixed model with outcome variance *σ*^2^=225 (*σ* = 15) and intraclass coefficient ICC=0.6 [32], and with significance level *a* = 0.05 and power = 1−b = 0.80, allowing for unequal group sample sizes (randomized 1:2), a total sample size of 134 patients is needed [64, 65]. Allowing for 20% attrition, a total of *n* = 168 patients (*n* = 56 waiting list, *n* = 112 treatment) will be included.

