## Assignment of interventions: allocation

### Sequence generation {16a}

The trial will use an allocation ratio of 1:1:1. Participants will be stratified by age in two categories 12–14 years of age and 15–17 respectively. Block randomization will be used with variable block sizes. To reduce predictability of a random sequence, the block sizes are made with random block sizes in Stata version 18 [66] by a statistician, and neither the research team, the clinicians or the administrative team have access to this information at any point of the trial.

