### Methods in analysis to handle protocol non-adherence and any statistical methods to handle missing data {20c}

Linear mixed models, which tolerate missing values and minimize the loss of statistical power in case of drop-out, will be fitted using the maximum-likelihood estimation method and based on the intention-to-treat sample. Where relevant in other types of analyses, missing data will be handled using multiple imputation methods.

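### The primary SCAS change analysis is stated with no baseline adjustment and no age-stratum term; adjusting for baseline would lower its variance by about 20% on the plan's own inputs

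*Protocol article*

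**What the plan says.** Statistical methods {20a} gives the primary analysis as the association in which "the change in SCAS-C/P total score from pre- to post-treatment and trial condition will be analyzed using linear mixed model regression". It lists no covariates, and it neither includes nor excludes baseline or age group. The same section adds: "A more detailed analysis plan will be developed prior to the end of recruitment for both primary and secondary analyses".

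Sample size {14} uses the same measure, "detecting a difference of 10 points between the waiting list and the (combined) treatment groups in change in SCAS score". Its inputs are introduced by "Using a linear mixed model with outcome variance" (225, SD 15), "and intraclass coefficient ICC=0.6", and a significance level and power given as "0.05 and power = 1−b = 0.80".

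Sequence generation {16a} says "Participants will be stratified by age in two categories" (12–14 and 15–17 years), and Trial design {8} agrees. No analysis section mentions that stratum.

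The missing-data section {20c} relies on "Linear mixed models, which tolerate missing values and minimize the loss of statistical power in case of drop-out", fitted by maximum likelihood in the intention-to-treat sample.

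**The concern.** Randomisation makes the arms equal in expectation at baseline. An analysis that uses this fact is more precise than one that compares raw changes. The primary analysis as worded can be carried out in two natural ways that do not use it:

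- one change value per participant, compared between conditions;
- a mixed model with arm-by-time terms in which each arm has its own free baseline mean.

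Both give the change-score contrast. A baseline-adjusted analysis, or a mixed model with a common baseline mean, answers the same question from the same data with a smaller standard error. It also takes chance baseline imbalance out of the individual estimate.

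The comparisons with the fewest participants stand to gain most: each active arm against waitlist, and planned against on-demand feedback. The Discussion presents the second of these as a strength of the design, but Sample size {14} sizes only the pooled treatment groups against waitlist.

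**Working it through.** **Inputs**, all from Sample size {14}: variance σ² = 225, ICC ρ = 0.6, difference 10 points, α = 0.05 (two-sided assumed, since sidedness is not stated), power 0.80, ratio 1:2, attrition 20%. I take the ICC as the pre–post correlation and assume equal variance at both times.

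**1. The plan's own figure.** A two-sample t-test for 10 points, SD 15 and ratio 1:2 needs 28 + 56 = 84. Multiplying by 1 + (2 − 1) × 0.6 = 1.6 gives 134.4, i.e. 134. Then 134 / 0.8 = 167.5, i.e. 168. Both stated totals are reproduced. The route is inferred, because the article prints no formula. On this route the ICC inflates the sample size, so no credit was taken for the pre–post correlation.

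**2. Variance per participant.**
- Change score: 2σ²(1 − ρ) = 2 × 225 × 0.4 = 180.
- Adjusted for baseline: σ²(1 − ρ²) = 225 × 0.64 = 144.
- Ratio 144/180 = 0.80. The standard error ratio is √0.80 = 0.894, about 11% smaller.

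**3. Standard errors** with 134 analysed, SE = √[V(1/n₁ + 1/n₂)]:

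| Comparison | Change (V = 180) | Adjusted (V = 144) |
|---|---|---|
| Waitlist vs pooled treatment, 45 vs 89 | 2.45 | 2.19 |
| Any two single arms, 45 vs 45 | 2.83 | 2.53 |

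**4. Power for 10 points.** Pooled comparison (noncentral t, 45 vs 89): 98.1% with change, 99.5% adjusted. One active arm against waitlist (normal approximation, about 45 per arm): about 94% and 98%. At 45 vs 45 the smallest difference detectable with 80% power, 2.80 × SE, falls from about 7.9 to 7.1 points.

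**5. Dependence on the ICC.** The proportional reduction is 1 − (1 − ρ²)/[2(1 − ρ)] = (1 − ρ)/2:

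| ICC | 0.4 | 0.5 | 0.6 | 0.7 | 0.8 |
|---|---|---|---|---|---|
| Variance reduction | 30% | 25% | 20% | 15% | 10% |

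**6. Does a mixed model settle this by itself?** No. In 300 simulated trials (45 vs 89), a mixed model with free baseline means gave exactly the change-score estimate, with variance 6.63. A mixed model with a common baseline mean and an analysis of the post score adjusted for baseline had almost equal variances (5.37 and 5.39). Theory gives 180 × (1/45 + 1/89) = 6.02 and 144 × (1/45 + 1/89) = 4.82. The simulated ratio, 5.37/6.63 = 0.81, agrees with the 0.80 of step 2.

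**7. Age stratum.** The article gives no association between age and SCAS, so no gain can be calculated.

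**The case against.** The strongest objection is that {20a} expressly leaves detail to a later analysis plan that is not shown. Covariates and the parameterisation of a mixed model usually belong there, and a journal article is condensed. Silence is not exclusion. A mixed model with a common baseline mean also fits the wording of {20a}, and the additional analyses in {20b} already treat pre-treatment as a modelled occasion. This stands: the article contains no error here, and the analysis plan may already settle the matter. What remains is that {20a} fixes the contrast as change by condition, and a mixed model fitted to that wording does not gain the precision unless the constraint or covariate is specified.

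The practical effect on the main test is small, at 98.1% against 99.5% power. This also stands.

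A reader might draw stronger conclusions that the documents do not support:

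- **That {20a} contradicts {20c}.** If each participant had a single change value, anyone without a post score would have no outcome, and the mixed model could not tolerate that loss. The conflict arises only on that literal reading. The mixed-model ICC in {14}, the time points in {20b} and the likelihood fitting in {20c} all suggest repeated scores.
- **That the estimate is biased.** Under randomisation the unadjusted change contrast is unbiased. Chance imbalance is part of its standard error, not an additional defect.
- **That the sample size depended on this precision.** The inferred route to 134 took no credit for the correlation.
- **That omitting the age stratum invalidates the intervals.** If age is related to SCAS, omission makes them somewhat too wide, which is conservative.

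**Conclusion.** The point holds as a recommendation on precision. As worded, the primary analysis can be carried out in ways that carry 25% more variance than necessary (180 against 144); put the other way, adjustment removes 20% of the change-score variance and about 11% of the standard error. This rests on ICC 0.6 acting as the pre–post correlation, on equal variances at the two times, and on the analysis being an unadjusted change contrast or having free baseline means. If the analysis plan already specifies a common baseline mean or baseline adjustment, nothing is lost.

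The pooled comparison hardly needs the gain. It is most useful for each active arm against waitlist and for planned against on-demand feedback, where the standard error falls by 0.30 points (2.83 to 2.53). The age-stratum part is a request to analyse as randomised, with no size attached.

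**What to change.** State in {20a} or the analysis plan that pre- and post-treatment SCAS are modelled as repeated outcomes in one mixed model, with a common baseline mean across the three arms, arm effects at post-treatment, a participant random intercept, and age stratum (12–14, 15–17) as a fixed effect. Participants with only a baseline score then stay in the likelihood, so the statement on missing values in {20c} holds.

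The post score adjusted for baseline and age stratum is an acceptable alternative with practically the same precision. It needs a post score, or imputation, for each participant.

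Adjusting the YODA logistic model is optional. Doing so turns the odds ratio into a conditional one, so it should be reported as such or standardised to a marginal effect.

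The cost is wording only. Both variables are already collected, and the sample size does not change. The choice should be fixed before outcome data are compared by arm.

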### Objectives {7}

The primary aim of the study is to examine the effectiveness of CoolMinds, an Internet-delivered cognitive behavioral therapy intervention, among adolescents aged 12–17 years. Specifically, the study seeks to examine the effectiveness of CoolMinds when administered with either planned feedback or on-demand feedback from a therapist, compared to a waitlist control group. Furthermore, the study will explore the effectiveness of delivering one booster session compared to no booster session in enhancing treatment outcomes.

We hypothesize that a higher proportion of participants in the two treatment conditions will achieve recovery from their primary anxiety diagnosis compared to those in the waitlist control group. Additionally, both treatment conditions are hypothesized to result in greater reduction in anxiety symptoms compared to the waitlist control group. We also hypothesize that the booster session will increase and better maintain reduction in anxiety symptoms over time.

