#### Secondary outcomes

The secondary outcomes consists of point differences in anxiety diagnosis and severity measured by clinician-review Youth Online Diagnostic Assessment-Child and Parent Versions (YODA) [48]. YODA is an online diagnostic assessment tool that assesses DSM-5 anxiety disorders and specific phobias based on the *Anxiety and Related Disorders Interview Schedule for DSM-5*, which is considered the golden standard [49]. The YODA uses yes/no responses to closed-ended questions, as well as open-ended questions that require written descriptions of cognitions, behaviors and impact on functioning [48]. The YODA is completed separately by the adolescent and the parents, and a clinical psychologist trained in the assessment of adolescent anxiety disorders then reviews and evaluates the responses to determine the diagnosis and symptom severity.

Point differences in anxiety symptoms interference on daily life measured by the self- and parent-reported questionnaire Child Anxiety Life Interference Scale (CALIS) [46]. CALIS [50] is used to measure the impact of youth anxiety on various areas of life functioning such as school, extracurricular activities, family life and friendships. The impact is evaluated separately by adolescents and their parents. In addition, parents rate the degree of impact on their own lives. CALIS has shown satisfactory internal consistency and moderate test-retest reliability [50].

Point differences in depressive symptoms are measured by The mood and Feelings Questionnaire (MFQ) [51]. MFQ is used to screen for depression in youth, both in epidemiological samples and in clinical samples, it is recommended as a self-report screening tool in secondary care [51]. The MFQ is completed separately by the adolescent and a parent. The MFQ has been validated in a Danish population sample of adolescents and shown excellent internal consistency [52].

Point differences in Quality of life is measured by EuroQol-5 Dimension Youth (EQ-5D-5L) [52], a 5-item self-report questionnaire assessing quality of life and self-rated health. The items cover five domains: mobility, self-care, usual activities, pain/discomfort, and anxiety and depression [53].

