### Methods for additional analyses (e.g., subgroup analyses) {20b}

A large number of additional analyses will be conducted. Logistic regression will be used to analyze associations between treatment arms and the secondary outcome YODA (dichotomized) at 3-month follow-up post treatment as well as each of the 20 NEQ items at post-treatment. Linear mixed model regression will be used to analyze associations between treatment arms and the following outcomes through all time points from pre-treatment to 12-month follow-up post treatment: SCAS-C score, CALIS, MFQ score by adolescent, SCAS-P, CALIS, MFQ score by parent, EQ-5D-5L score, CSQ-8 score, and SUS score. Furthermore, linear mixed model regression will be used to analyze associations between treatment arms and WAI-SF at treatment sessions 2, 4, 6, 8, and 10 and at post treatment, and between treatment arms and weekly measures of CAS-8 and S-MFQ. Linear regression will be used to analyze associations between treatment arms and WAI-TECH-SF and engagement at post-treatment, as well as the cost-effectiveness analysis.

Finally, we wish to conduct a post hoc exploratory growth mixture model that can provide trajectories of change in symptoms through the trial across the different sessions and post-measurements.

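### The first hypothesis is about losing the primary anxiety diagnosis, but the planned YODA analysis splits a total score at 1 that the protocol never ties to that diagnosis

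*Protocol article*

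**What the plan says.** Objectives {7} states the first hypothesis as follows: "a higher proportion of participants in the two treatment conditions will achieve recovery from their primary anxiety diagnosis", compared with the waitlist. The outcome is specific to one disorder per participant, the primary one.

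Statistical methods {20a} gives the corresponding binary analysis: "the association between YODA, dichotomized as YODA total score" at least 1 versus below 1, "and the three trial conditions at post-treatment will be analyzed using logistic regression". Section {20b} applies logistic regression again to "the secondary outcome YODA (dichotomized) at 3-month follow-up post treatment".

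The Secondary outcomes section describes the instrument: "YODA is an online diagnostic assessment tool that assesses DSM-5 anxiety disorders and specific phobias". A clinical psychologist "reviews and evaluates the responses to determine the diagnosis and symptom severity". That section gives no total score, no scoring range and no meaning for a value of 1. It describes the YODA outcome as point differences, not as recovery.

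Eligibility criteria {10} require a principal anxiety diagnosis. None of the nine exclusions concerns a further anxiety disorder.

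**The concern.** The hypothesis names an event, and the analysis names a cut on a score. The protocol does not say that they coincide. Participants with more than one anxiety disorder are eligible and YODA covers several disorders, so a total across the instrument need not track the primary diagnosis. An adolescent could lose the primary diagnosis, keep a second one, and be counted as not recovered.

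The post-treatment logistic regression is the only planned test of the first hypothesis. The waitlist group leaves the study after its post-waitlist measures (Trial design {8}), so the 3-month repeat cannot test it. If the variable is stricter than the hypothesis, the odds ratio answers a different question, and a null result could be misread as failure to recover from the principal disorder.

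**Working it through.** **Plan's own figures.** The protocol gives no recovery rate, comorbidity rate or power for YODA. The sample size rests on SCAS alone. The 134 participants needed, divided by 0.80 for attrition, give 167.5, rounded up to 168. YODA does not enter this calculation.

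**What a score below 1 could mean.**
- *Count of diagnoses over YODA's disorders:* free of every anxiety diagnosis. This implies loss of the primary diagnosis, but the reverse does not hold. The two endpoints agree for anyone with no other anxiety disorder.
- *Sum of severity or symptom ratings:* almost no residual symptoms. This is stricter again, because symptoms below diagnostic level count as failure.
- *A code or rating for the principal diagnosis only:* this could match the hypothesis, but it is hard to reconcile with the word total.

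**Illustration for the count reading.** All rates below are assumptions.
- Analysed numbers: 80% of 56 is 44.8, taken as 45 waitlist; 80% of 112 is 89.6, taken as 90 treated.
- Recovery from the primary diagnosis, p: 40% treated and 15% waitlist; as a second scenario, 50% and 20%.
- Share of recovered participants who keep another anxiety diagnosis, k, equal in both groups. It is the share with another disorder times the probability that this disorder persists: 0.3 × 0.3 = 0.09; 0.5 × 0.5 = 0.25; 0.7 × 0.7 = 0.49.

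The rate on the stricter endpoint is p(1 − k). With rates pT and pW, difference d = pT − pW and pooled rate p̄ = (45pW + 90pT)/135:

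SE0 = √[p̄(1 − p̄)(1/45 + 1/90)], SE1 = √[pW(1 − pW)/45 + pT(1 − pT)/90], power = Φ[(d − 1.96·SE0)/SE1], two-sided 5%.

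For k = 0: p̄ = 0.3167, SE0 = 0.0849, SE1 = 0.0742, so power = Φ[(0.25 − 0.1665)/0.0742] = Φ(1.13) = 87%.

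For k = 0.25: rates 0.30 and 0.1125, p̄ = 0.2375, SE0 = 0.0777, SE1 = 0.0675, so power = Φ[(0.1875 − 0.1523)/0.0675] = Φ(0.52) = 70%.

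| k | Treated | Waitlist | Difference (points) | Power, 40% vs 15% | Power, 50% vs 20% |
|---|---|---|---|---|---|
| 0 | 40.0% | 15.00% | 25.00 | 87% | 94% |
| 0.09 | 36.4% | 13.65% | 22.75 | 82% | 90% |
| 0.25 | 30.0% | 11.25% | 18.75 | 70% | 80% |
| 0.49 | 20.4% | 7.65% | 12.75 | 47% | 55% |

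The rates and differences shown are for the 40% vs 15% scenario.

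Section {20a} names three conditions, so a pairwise contrast of about 45 against 45 is also relevant. With 50% vs 20% and k of 0, 0.30 and 0.50, power is 94%, 75% and 54% at 90 vs 45, and 86%, 64% and 46% at 45 vs 45.

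No calculation was made for the severity reading, because the documents give no score distribution.

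**The case against.** A reader might infer that the analysis does not measure the hypothesised outcome at all, or uses the wrong variable. The documents do not support that. The total score is undefined, so what the cut captures cannot be settled from the text. On the count reading, everyone below 1 has also lost the primary diagnosis, which makes it a conservative form of the same outcome. A score for the principal diagnosis alone is unlikely but not excluded.

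A reader might also infer a definite loss of power. That does not follow either. With no persisting second diagnosis there is no loss, and at k = 0.09 the loss is about five points. The model also assumes equal persistence in both groups.

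Section {20a} promises a more detailed analysis plan before recruitment ends, and deriving a score is ordinary material for such a plan. That disposes of any complaint that the scoring detail is missing. It does not dispose of the mismatch, because the protocol has already fixed the variable and the cut. A plan that follows them inherits the problem. A plan that departs from them changes a published endpoint in a trial whose clinicians and research team are unblinded ({17a}).

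Finally, the outcomes and methods sections treat YODA as secondary, although the abstract lists it among the primary outcome measures. This limits the consequences, but the first hypothesis still depends on this analysis.

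**Conclusion.** The point holds as a mismatch between hypothesis and endpoint. The protocol hypothesises recovery from the primary diagnosis, fixes a cut on a total score, and never links the two. On the two more natural readings of the total, the planned endpoint is related to the hypothesised one but stricter.

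The size cannot be fixed from the documents. Under the assumed 40% vs 15% recovery with 90 and 45 analysed, power runs from 87% (no loss) down to 47% as the share keeping another diagnosis rises from 0 to 49%. These figures show what is possible and do not predict what will happen. The SCAS primary analysis and the total of 168 are unaffected. The correction is worth making because it is cheap and settles what the odds ratio means.

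**What to change.** In sections {20a} and {20b}, replace the split of the total score with a binary endpoint defined as: the principal anxiety diagnosis recorded at baseline is no longer met on clinician-reviewed YODA. Use it in the post-treatment and the 3-month logistic regressions. Report freedom from all anxiety diagnoses as a separate secondary outcome. Align the YODA entry under Secondary outcomes, which now speaks of point differences, with this definition.

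The cost is a wording change, one derived variable and one extra reported outcome. No new data are needed, since the psychologist already determines diagnosis and severity from YODA. The change should be dated and recorded openly as an amendment.
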